## Abstract

Evidence-based practice (EBP) combined with quality of care improves patient outcomes. However, there are still difficulties for its implementation in daily clinical practice. This project aims to evaluate the impact of the incorporation of the Advanced Practice Nurse (APN) role on the implementation of EBP at three levels: context, nurses’ perceptions, and clinical outcomes. Mixed-methods study in two phases is proposed. Phase 1: a quasi-experimental design where five APNs are included in five hospitalization wards that are compared with another five similar wards without APNs. Variables from Practice-Environment-Scale-Nursing-Work-Index, Health-Science-Evidence-Based-Practice-Questionnaire, and Advanced-Practice-Nursing-Competency-Assessment-Instrument are used. Clinical outcomes are followed-up with monthly. A descriptive and exploratory analysis is performed. Phase 2: an exploratory qualitative design through focus groups at the intervention wards after one year of APNs implementation. Explicative data are gathered to explain the progression of change and how actors perceive and attribute triggers, barriers, and facilitators for change. An inductive thematic analysis is performed. The inclusion of APN in hospitalization context is insufficiently studied. It is hoped that these figures provide solutions to the multiple barriers in the development of EBP in these sceneries and contribute to resolve the gap between research results and healthcare practice.

## 1. Introduction

Evidence-based clinical practice (EBCP) has become an essential tool for the improvement of decision-making in health care [1,2,3]. Despite the widespread acceptance of this concept as a paradigm on which to base decisions in daily clinical practice [4], nearly 35% of these decisions do not conform to the recommendations offered by the best scientific evidence [5]. Multiple factors hinder the incorporation of best evidence into clinical practice [6,7,8], being an arduous and multifactorial task [9,10]. The volume of evidence and its variability is growing considerably, making it unmanageable for the clinician [11]. In addition, there is a delay in the implementation of research results caused by a resistance to change and the perception of clinical judgment as the core element in decision-making [12]. These facts may reduce the credibility of clinical practice guidelines (CPG) [13] and therefore increase the difficulty of their implementation, causing a suboptimal adherence to recommendations [13].

Health care systems have focused on minimising the variability of clinical practice [14]. Research agencies have conducted strategies worldwide for the effective transference of knowledge [15]. However, few proposals have taken into account the context and the organizational climate as relevant factors for change [16,17] and improvement of clinical outcomes [14,18]. The theory of planned behaviour (TPB) [19] and the Promoting Action on Research Implementation in Health Services (PARIHS) framework [20,21,22] are theoretical approaches underpinning the organisational change and facilitating the adherence to clinical practice guideline recommendations. In order to implement this theoretical model, attention should be focused on the facilitator role of the best evidence played by the Advanced Practice Nurse (APN) [23,24]. This approach would address two attention levels: individual, seeking to modify the work patterns of health care personnel; and organisational to facilitate this change.

In both of these approaches, a facilitating element can be characterised as an agent of change that predominantly uses a participatory problem-solving method rather than prescribing and directing a system of actions [25,26]. One of the solutions that is gaining the most popularity worldwide is to recruit APNs, whose high-level postgraduate training and advanced knowledge and skills make them very appropriate for this task, to raise the level of EBCP within a given environment. In this respect, studies performed in different contexts have acknowledged the value of APNs as agents of change [27,28], capable of influencing their work environment through the transfer of evidence-based knowledge and thus producing disruptive innovation [29]. These nurses are especially well qualified for this task because their professional practice is based on competencies related to research and EBCP, acting as leaders in their context regarding the adoption of updated clinical practices [30]. It has been shown that optimising nurses’ contributions to health care by expanding their capabilities and scope of practice is an effective strategy for improving the overall quality of health services [31,32,33]. The work performed by APNs is safe, effective, and well received by users [34].

This project represents an initial experience to explore possible care improvements for the future application of the functions of the advanced practice hospitalization nurse (APHN) in our health system. For this intent, we propose APNs be incorporated into hospital wards as a new approach to the role of advanced practice nursing in our country. By doing so, we assess the value of this new role—one that puts into practice the clinical leadership—and the process of incorporating that role within the team from the perspective of the nurses involved. Moreover, the elements of the PARIHS framework are taken into account as a facilitating element of behavioural change based on the TPB for the implementation of EBCP within a favourable context supported by the health care agency.

Therefore, the main objective of this study is to evaluate the impact of the incorporation of the APHN role compared to hospital wards without APHN role. The specific objectives are to (1) evaluate the impact of APHNs on the EBCP environment (contextual and individual factors); (2) explore the bedside nurses and APHNs’ perceptions towards EBCP concerning the incorporation of the APHNs in their hospital ward; (3) determine the impact of APHN-directed interventions on clinical outcomes of inpatients; and (4) assess the competencies of the APHNs who take part in the project.

## 2. Materials and Methods

### 2.1. Design

This protocol describes an ongoing project, currently at the intervention stage, consisting of a mixed-methods study in two phases with a first quasi-experimental design and a second exploratory qualitative phase through focus groups (Figure 1).

### 2.2. Settings

Ten medical and surgical hospital wards were selected in three public hospitals managed by the Balearic Islands health service—a university hospital and two regional hospitals. Intervention and control groups were created, each consisting of three medical and two surgical wards.

### 2.3. Interventions

The nurse who develops the role of APHNs was replaced by another registered nurse who assumes the habitual assignment of patients. The replacement of the five nurses was covered by the Health Service of the Balearic Islands (IB-Salut) who gave financial support to the project in these terms. Two registered nurses were selected from each unit (one APHN and one support nurse) and, together with the ward’s supervisor, received specific training (Table 1) in line with the theoretical framework of the project and the competencies required [30]. All APHNs were monitored and advised by the research team via individual contact as necessary and at monthly meetings between the research team, the APHNs, the support nurses, and the supervisors. The support nurse (whose normal assignment of patients was maintained) and the supervisor assisted with, in conjunction with the APHN, the introduction of new work dynamics to improve the environmental outcomes within the ward. The APHNs designed specific actions to put into effect two clinical practice guidelines (CPG), adapted as appropriate to the specific context and its characteristics The selection of the CPGs was based on the following criteria: (1) the number of guidelines was limited so that the APHN-directed interventions could be designed and monitored within the study period; (2) CPG topics had to be standard and applicable to any of the intervention wards regardless of patient or team characteristics; (3) CPG topics had to be of high impact in inpatient health and aligned with the Health Service’s strategic map. Therefore, the selected guidelines were “Care and maintenance of vascular access to reduce complications” [35] and “Prevention and treatment of pressure ulcers” [36].

The APN group, together with the support nurses and supervisors, are in frequent contact through meetings, initially weekly and later monthly. Here, they can assess each other’s progress and, with the research team, share material, exchange ideas and experiences, and ensure that the research data are obtained correctly.

In the control wards, no intervention was performed to improve or facilitate the usual pattern of treatment. The indicators measured were the same as in the intervention wards, enabling us to compare the results obtained in each case.

### 2.4. Variables

In the quantitative phase, four main study variables are addressed via Spanish validated instruments (Supplementary Appendix 1):-Organisational traits, measured by the Practice Environment Scale Nursing Work Index (PES-NWI) [37].-The nurses’ individual level of EBCP, measured by the Health Science Evidence-Based Practice Questionnaire (HS-EBP) [38].-Health indicators of the patients admitted to the study wards, derived from the clinical practice guidelines implemented by the APHNs in their wards and obtained by monthly clinical audits (Table 2).-The APHNs’ competence, as measured by the Advanced Practice Nursing Competency Assessment Instrument (APNCAI) [39].

In the qualitative phase, after 1 year of the APHN’s implantation, the nurses’ perceptions are explored regarding the evidence-based clinical practice and the impact on the health results of the patients (Table 2).

### 2.5. Sample and Participants

The quantitative phase started with registered nurses working in the hospital wards included in the study in addition to the APHNs and their supervisors working in the intervention wards. The qualitative phase is carried out only with the nurses of the intervention group, the APHN, and the supervisors.

The sample size needed for the quantitative phase was calculated according to the difference of expected scores of the PES-NWI questionnaire on organizational traits (Supplementary Appendix 1). The calculation was performed for independent means, assuming an alpha risk of 0.05 and a beta risk of less than 0.2 in bilateral testing. Therefore, to detect a difference equal to or greater than four points, 70 subjects are needed in each of the study groups, assuming a standard deviation of eight and a loss rate of 10%. In the Health Service of the Balearic Islands, there are about 15 nurses per hospital unit, thus each study group corresponds to five hospital wards.

In the qualitative phase, six focus groups are carried out: one focus group with the APHNs and five focus groups with nurses, one in each of the five units where the figure of the APHN is implanted. Sampling for the focus groups of nurses is intentional, and a minimum of six and a maximum of 12 nurses are recruited in each of the units. The five APHNs and at least three to five support nurses are included in the APHN focus group.

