### 2.6. Inclusion and Exclusion Criteria

Quantitative phase: the intervention wards were selected according to the baseline score obtained in the PES-NWI questionnaire, although no cut off points were established. Medical and surgical wards with a well-established leadership structure were included with the participation of each hospital’s nursing managers. Each intervention unit was paired with a control unit in the same hospital with similar characteristics and health indicators.

After the selection of hospital wards, project information meetings were held for the nursing teams, who were invited to participate. The nurses in each unit nominated one of their number, presenting the competencies needed to perform the role of the APHN, and another who provided support. Both participants had to be in a stable employment relationship in the unit. This selection was made from the nurses who applied to take part, according to their leadership qualities and APNCAI scores obtained (Supplementary Appendix 1). The supervisors of the wards were also part of the study subjects.

Qualitative phase: for the focus groups in the intervention groups, we select registered nurses who have worked throughout the entire intervention period. For the APHN focus group, the inclusion criteria is having been the APHN of the unit from the beginning of the project.

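### The quantitative sample names the staff who deliver the intervention for one arm only, and nothing keeps their PES-NWI and HS-EBP scores out of the arm comparison

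*Protocol article*

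**What the plan says.** Section 2.5 of the protocol article builds the quantitative sample from the registered nurses of all ten wards, "in addition to the APHNs and their supervisors working in the intervention wards". These added staff are named for one arm only. Section 2.6 is wider on supervisors: "The supervisors of the wards were also part of the study subjects". It does not say of which arm.

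Section 2.3 describes who delivers the change: "Two registered nurses were selected from each unit (one APHN and one support nurse) and, together with the ward’s supervisor, received specific training". The support nurse keeps a normal patient load and so remains one of the ward nurses. The APHN's post is backfilled: "The nurse who develops the role of APHNs was replaced by another registered nurse who assumes the habitual assignment of patients". Under section 2.6 the APHN and support nurse were chosen from applicants "according to their leadership qualities and APNCAI scores obtained". For the other arm, section 2.3 states: "In the control wards, no intervention was performed to improve or facilitate the usual pattern of treatment".

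Section 2.4 uses PES-NWI for organisational traits, HS-EBP for nurses' individual level of evidence-based practice, and APNCAI for the APHNs' competence. Section 2.7 gives the measurement dates but not which staff complete PES-NWI and HS-EBP for the comparison. Section 2.8 lists as possible confounders age, gender, hospital, unit, years of experience and academic qualifications. Role in the intervention is not among them.

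**The concern.** Specific objective 1 is the effect of APHNs on the ward's evidence-based practice environment, both contextual and individual. APHN competence is a separate objective with its own instrument. If the people who deliver the change are averaged with those meant to receive it, the two questions mix.

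On PES-NWI, the APHN, support nurse and supervisor would be rating an environment that they were charged with improving. On HS-EBP, they would be answering about material that their own training covered (Table 1 includes evidence-based practice concepts, critical reading and research methods). Part of any arm difference could then reflect the course and the selection of its participants, even if no bedside nurse changed. Nothing in the listed adjustment would remove it, and the likely direction favours the intervention.

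**Working it through.** **The plan's own figure.** Inputs from section 2.5: difference 4, SD 8, two-sided alpha 0.05, power 80%, loss 10%.

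n = 2 × [8 × (1.960 + 0.842) / 4]² = 62.8, so 63 per group; 63 / 0.9 = 70. The stated 70 per group reproduces, and this point does not affect it.

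**Head counts.** About 15 nurses per ward × 5 wards = 75 per arm. Delivering staff in the intervention arm: 5 APHNs + 5 support nurses + 5 supervisors = 15. The denominator depends on who is counted:
- 75 if the delivering staff are taken as already inside that figure
- 80 if the 5 supervisors are added
- 85 if the 5 supervisors and the 5 replacement nurses are added

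**Shift if pooled.** Shift = (m / N) × excess. Here m is the number of delivering staff, N the number in the intervention arm, and excess the amount by which their mean exceeds that of the other nurses. The documents give no excess, so 4, 8 and 16 points (0.5, 1 and 2 SD) are assumed.

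| Group pooled | m / N | Excess 4 | Excess 8 | Excess 16 |
|---|---|---|---|---|
| APHNs + supervisors | 10/75 = 13.3% | 0.53 | 1.07 | 2.13 |
| APHNs + supervisors | 10/85 = 11.8% | 0.47 | 0.94 | 1.88 |
| All three roles | 15/80 = 18.8% | 0.75 | 1.50 | 3.00 |
| All three roles | 15/85 = 17.6% | 0.71 | 1.41 | 2.82 |

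At an excess of 8 points the shift is 0.94 to 1.50 points, which is 24% to 38% of the 4-point target. To produce the full 4 points alone, the delivering staff would need an excess of 4 × 75/10 = 30 points (10 of 75) or 4 × 80/15 = 21.3 points (15 of 80).

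**Effect on the test if no other nurse changes.** With 63 per group, SE = 8 × √(2/63) = 1.425. The two-sided rejection rate is 1 − Φ(1.96 − b/SE) + Φ(−1.96 − b/SE), where b is the shift. It is about 0.066 at b = 0.53, 0.117 at b = 1.07 and 0.18 at b = 1.5, against a nominal 0.05.

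**Power if the delivering staff are left out.** Power = Φ(4/SE − 1.96), with SE = 8 × √(1/n₁ + 1/n₂) and nurses treated as independent, as the protocol's sizing does.
- 65 v 75 (75 less 5 APHNs and 5 support nurses; supervisors were never in the 75): SE = 1.356, power about 84%. After 10% loss, about 58 v 68: SE = 1.430, power about 80%.
- 60 v 75 (all 15 taken out of the 75): about 82%. After loss, 54 v 68: about 78%.

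**The case against.** A reader might infer that these scores do shift the comparison. The article does not say so. Section 2.5 lists who takes part in a phase with four main variables, and the APHNs have to appear there for the APNCAI alone. Pooling is a possible consequence of the wording, not a stated plan, so the shift is conditional.

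A reader might also infer that the control arm is registered nurses only, with no equivalents of the added staff. That is too strong. Section 2.6 can be read to include control supervisors. APHNs and support nurses were ordinary ward nurses before selection, so nurses of the same kind work unlabelled in the control wards. None of those counterparts was trained or delivered the intervention, however.

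Three further arguments deserve an answer:

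- *Analysis sets belong in an analysis plan.* That is fair for a silent article. Here the article itself states an arm-asymmetric sample and words the supervisors differently in two sections, so there is text to correct.
- *A whole-team comparison is legitimate.* The main objective compares wards with and without the role, so the all-respondent result has a place. It does not isolate the effect on the nurses the APHN is meant to influence.
- *Excluding the deliverers creates the opposite imbalance.* This stands in part. Removing nurses chosen for leadership and APNCAI scores from one arm, while their counterparts stay in the other, makes post-intervention levels non-comparable. Change from baseline or baseline adjustment deals with most of this, but not necessarily all.

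**Conclusion.** The point holds in conditional form. The sample definition is asymmetric by arm, sections 2.5 and 2.6 do not agree clearly on supervisors, and no stated rule or adjustment separates deliverers from recipients on PES-NWI and HS-EBP. Support nurses matter here too: setting aside only APHNs and supervisors would leave five trained deliverers in the intervention mean.

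The calculated size rests on pooling and on an excess that the documents do not give. Over the assumed range, the bias could be a material part of the target difference but would not plausibly account for all of it. The points scale applies to PES-NWI; HS-EBP is exposed in the same way, but the article gives no SD or target from which to size it. The point is worth correcting before analysis and does not undermine the design.

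**What to change.** 1. Reconcile sections 2.5 and 2.6 on whether control-ward supervisors are study subjects.
2. State that the main PES-NWI and HS-EBP comparison is between bedside registered nurses in both arms. Exclude APHNs, support nurses and supervisors (control supervisors too, if surveyed) at both time points and report them separately. Say how the five replacement nurses are classed.
3. Base that comparison on change from baseline, or adjust for baseline, rather than on post-intervention levels alone. Section 2.7 already provides pre-intervention measurements of both instruments.
4. Show the all-respondent result as a sensitivity analysis.

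The cost is a short population statement and about 10 fewer intervention nurses, with the modest loss of power shown above. The coded questionnaires must carry each respondent's role. A residual selection asymmetry remains, because the control wards' natural leaders cannot be identified and removed; the report should acknowledge it.

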### 2.8. Data Analysis

Descriptive and exploratory analyses of the quantitative data will be performed, determining, among other parameters, the main indices of central tendency, dispersion, and shape. In addition, an analysis of missing values will be conducted. The association between variables will be determined according to the scale of their mean values. A stratified analysis will be carried out using the Mantel and Haenszel test, among others (stratifying according to the possible confounding variables). Bivariate analysis will be performed to detect significant associations between the main variables and sociodemographic, occupational, and complementary variables. Multivariate analysis will also be carried out using regression models. The mean values obtained will be compared by ANOVA or the nonparametric equivalent (Kruskal–Wallis test). The main variables will be crossed with the sociodemographic variables (age, gender), the occupational variables (hospital, unit, years of experience as a registered nurse), and the complementary variables (academic qualifications). These will be analysed as possible confounders and/or modifiers of the effects produced on the study variables. Finally, an exploratory analysis of lost data will be performed. The SPSS v.22 statistical software package ( SPSS Inc., Chicago, IL, USA) will be used for all these analyses.

For the qualitative phase, a realistic thematic analysis [40] of the focus groups transcriptions will be carried out. It will be used to generate a rich description of registered nurse and APHN views on how the change process evolved and impacted the unit and patients’ outcomes and how context jeopardized and/or facilitated the process. Two researchers will analyze the data across five phases: (1) through a first process if reading, initial themes and codes will be identified and grouped and emerging patters will be checked; (2) a second process of reading and re-reading, aimed at interpreting the themes, will be conducted; (3) at this point, the two researchers will share their interpretation and will reach consensus on the list of codes and sub-codes; (4) these codes will be rechecked through a third process of reading then pieces of text that exemplify the themes will be categorized under each code. Attention will be paid to new codes that may not have been identified earlier; (5) final patterns and links will be identified among themes and codes.

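### The sample size treats nurses as independent although whole wards (5 against 5) receive the APHN, and no named analysis is stated to account for wards, so the stated power is not a property of this design

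*Protocol article*

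**What the plan says.** The abstract gives the unit of assignment: "five APNs are included in five hospitalization wards that are compared with another five similar wards without APNs". Section 2.2 confirms it: "Intervention and control groups were created, each consisting of three medical and two surgical wards". Section 2.6 adds that each intervention ward is matched to a control ward of the same hospital.

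Section 2.5 derives the sample size from PES-NWI scores: "The calculation was performed for independent means, assuming an alpha risk of 0.05 and a beta risk of less than 0.2 in bilateral testing". The result is that "to detect a difference equal to or greater than four points, 70 subjects are needed in each of the study groups", with an SD of 8 and 10% loss. Ward size is used only to turn nurses into wards: "there are about 15 nurses per hospital unit, thus each study group corresponds to five hospital wards".

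For the analysis, section 2.8 states "The mean values obtained will be compared by ANOVA or the nonparametric equivalent". It also names a Mantel-Haenszel stratified analysis and regression models whose form is not given. Ward appears once, within "the occupational variables (hospital, unit, years of experience as a registered nurse", among variables to be examined as possible confounders or effect modifiers.

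Section 2.7 places PES-NWI in January 2018 and September 2019, and HS-EBP in April 2018 and September 2019, so both scales have a baseline and a follow-up measurement.

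**The concern.** Nurses in one ward work under the same supervisor, with the same APHN or none, and PES-NWI asks them about that shared setting. The article itself treats the score as a feature of wards, because section 2.6 uses baseline PES-NWI to choose the intervention wards. Some within-ward correlation is therefore to be expected, and the evidence about the role rests on ten assigned units rather than on 140 separate nurses.

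Two things follow. The power in section 2.5 belongs to a design in which nurses are assigned individually, so a null result could be read as if the study had had 80% power for 4 points. And if the comparison of means is run on nurses without a ward term, its standard error is too small and its p-values overstate the evidence on a role that the health service may decide to retain.

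This is not a detail left to a fuller plan. The article states the independence assumption outright, and its own design contradicts it.

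**Working it through.** **Inputs.** From section 2.5: difference 4, SD 8, two-sided alpha 0.05, power at least 80%, loss 10%, five wards per group. From the abstract and section 2.2: whole wards, 5 against 5. The ICC is an assumption (0.01 to 0.10), because the documents give none.

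**Step 1, the plan's own figure.** n = 2 × (1.96 + 0.842)² × (8/4)² = 62.8, so 63 per group; 63/0.9 = 70. The stated 70 is reproduced (power 80.1% by the normal approximation) with a design effect of 1.

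**Step 2, allow for wards.** Analysed nurses per ward: m = 63/5 = 12.6. Design effect DE = 1 + (12.6 − 1) × ICC. Standard error of the difference = 8 × √(2 × DE/63). Power comes from the noncentral t distribution with 10 − 2 = 8 df and noncentrality 4/SE. The critical value is 2.306, and 80% power needs a noncentrality of 3.20, so the detectable difference is 3.20 × SE.

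**Step 3, type I error if wards are ignored.** Approximately 2 × [1 − Φ(1.96/√DE)].

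| Assumed ICC | DE | SE | 4/SE | Power, 8 df | Detectable difference | Type I error, wards ignored |
|---|---|---|---|---|---|---|
| 0 | 1.00 | 1.43 | 2.81 | 69% | 4.6 | 5.0% |
| 0.01 | 1.12 | 1.51 | 2.66 | 64.5% | 4.8 | 6.4% |
| 0.05 | 1.58 | 1.79 | 2.23 | 50% | 5.7 | 11.9% |
| 0.10 | 2.16 | 2.09 | 1.91 | 39% | 6.7 | 18.2% |

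A simulation of the individual-level t test with 13 nurses per ward (20,000 runs) gave type I errors of 6.5%, 12.2% and 19.2% at ICC 0.01, 0.05 and 0.10. With 15 nurses per ward and no loss, power on 8 df is 71%, 54% and 41%, so full response does not restore 80%.

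**Step 4, does listing *unit* as a confounder deal with this?** Each ward lies wholly in one arm.

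- In a comparison of follow-up scores alone, ward indicators determine arm, so the arm effect cannot be separated from them. A Mantel-Haenszel analysis stratified by ward has only one arm in each stratum.
- In a model of both waves, arm-by-time can be estimated with fixed ward effects. These remove stable ward differences only. Changes over time that differ between wards for reasons other than the APHN remain, and an individual-level residual does not reflect them.

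In neither case does adjusting for *unit* supply the missing ward-level error term.

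**The case against.** The case for the plan has several sound parts.

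- **Baseline and pairing.** The table is for an unpaired comparison of follow-up scores. As an illustration, assume a pre-post correlation of 0.5 that cuts all variance by 25% (1 − 0.5²). Power on 8 df becomes 77%, 62% and 49% at ICC 0.01, 0.05 and 0.10. That softens the shortfall without removing it. Pairing could also reduce variance, but a paired ward-level analysis has only 4 df; if it removed no variance, power would be 52%, 40% and 31%. Neither device is in the calculation or the named analysis.
- **Unspecified regression models.** Their form may be set out in a fuller plan and could include a ward term. So it is not shown that every planned analysis treats nurses as independent, only that none is stated to account for wards.
- **Unknown ICC.** A reader might infer that the false-positive rate is well above 5% as a matter of fact. The documents do not support that: at ICC 0.01 it is about 6%, and it becomes large only from about 0.05.
- **No within-ward information.** A reader might infer that a ward-adjusted effect can never be estimated. That is true for follow-up scores alone, but section 2.7 provides scores before and after.
- **Patients.** A reader might extend the figures to the clinical indicators. The calculation concerns nurses only, Table 2 defines the indicators as ward-type percentages and rates, and nothing says that patients will be pooled as independent.
- **Exploratory purpose.** The article calls the quantitative analysis descriptive and exploratory, and it dates the follow-up questionnaires to September 2019, so restating power does not change conduct. This makes section 2.8 the more consequential place. It does not make the stated power correct.

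**Conclusion.** The point stands in a limited form. The arithmetic behind 70 per group is right; the independence assumption under it does not fit a design that assigns five wards against five.

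For any positive ICC, power for 4 points is below what section 2.5 implies under its own inputs, and a test that ignores wards rejects too often. The size depends on the ICC: about 65% to 39% power and about 6% to 18% type I error for assumed values of 0.01 to 0.10, for an unpaired follow-up comparison with 63 analysed nurses per arm. At an ICC of exactly 0, the individual-level test would keep its 80%; the 69% in the table then reflects only the cost of working with 8 df.

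The numbers apply to PES-NWI. The same reasoning carries over to HS-EBP, for which no sample size is given. For the clinical indicators it is only a reason to state how wards will enter the comparison.

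**What to change.** **Section 2.8.** Analyse PES-NWI and HS-EBP with a linear mixed model:

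- arm as a fixed effect, or arm-by-time if both waves are modelled;
- ward as a random effect, plus ward-by-time if both waves are modelled;
- the baseline ward score and hospital or matched pair, as far as ten wards allow;
- small-sample degrees of freedom, such as Satterthwaite.

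Add a comparison of ward means, or of ward mean changes, as a check. Name *unit* as the cluster and take it out of the list of confounders. State that the monthly clinical indicators are compared with ward as the unit of analysis or as the cluster.

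**Section 2.5.** Keep the derivation of 70 as the individual-level figure, and add the power for 4 points, or the detectable difference, with five wards per arm over a stated ICC range. If baseline adjustment or pairing is credited, give the assumed correlation.

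**Cost.** Revised wording in two sections, a little more analysis, and a less favourable stated power. No extra wards or nurses are needed. Section 2.8 is written in the future tense, so the analysis can still be changed.
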